- - 1. Therapy for acute infection or other serious medical illnesses within 14 days prior to screening.

Note: Therapy for acute infection or other serious medical illnesses that overlaps with a main study visit will result in postponement of that study visit until the course of therapy is completed; postponement outside of the allowed study visit timeframe will result in study discontinuation.

- - 1. Pregnancy or breastfeeding during the course of the study.
    2. Hypotension, defined as systolic blood pressure < 90mmHg, at time of screening.

Note: Hypotension noted prior to brachial artery reactivity testing on each main study visit will result in study visit postponement of at least one day until systolic pressure is ≥ 90mmHg the morning of brachial reactivity testing; postponement outside of the allowed study visit timeframe will result in study discontinuation.

- - 1. Hypertension, defined as the receipt of any antihypertensive medication within 28 days prior to screening or systolic blood pressure > 160mmHg at screening.
    2. Receipt of anti-inflammatory agents (including, but not limited to, plaquenil, infliximab, etanercept, mycophenylate mofetil, sirolimus, tacrolimus, cyclosporine, pentoxifylline, thalidomide) within 28 days of screening.
    3. Receipt of investigational agents, cytotoxic chemotherapy, systemic or topical glucocorticoids (of any dose and including inhaled or nasal steroids), or anabolic steroids within 28 days of screening.

Note: Physiologic testosterone replacement therapy is not exclusionary.

- - 1. Receipt of lipid-lowering drugs (including prescription or over the counter ‘fish oil’ or omega-3 fatty acid supplements), aspirin, other NSAIDS, acetazolamide, anticoagulants, anticonvulsants, or thyroid replacements within 28 days prior to screening.
    2. Use of sildenafil, vardenafil, or tadalafil within 72 hours (before or after) of each main study visit.
    3. Active drug or alcohol use or dependence that, in the opinion of the investigator, would interfere with adherence to study requirements.

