If subjects are excluded due to the above criteria, they may be approached again in the future or have their study visit rescheduled within the allowable timeframe if these criteria are no longer applicable. Co-enrollment into other studies will be permitted provided no drugs prohibited on this study will be given in the other study/ies and that the required blood draws do not exceed safe limits when combined with those for this study.

We are specifically excluding subjects with diabetes, hypertension, and dyslipidemia requiring therapy at screening in these two studies in order to better evaluate the role of HIV as the primary determinant of endothelial dysfunction. However, we will not discontinue study participation if these criteria develop during the course of these trials for two reasons. First, this would limit generalizability as the development of diabetes, hypertension, and severe dyslipidemia with antiretroviral therapy is common in the HIV-infected population. Second, it is possible that reduction of inflammation by PTX may theoretically prevent insulin resistance, hypertension, and hypertriglyceridemia, which are important endpoints to capture in these trials.

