5.4.1 Prohibited Medications

- Aspirin or other non-steroidal anti-inflammatory drugs (NSAIDS)
  - Anti-inflammatory agents (including, but not limited to, plaquenil, infliximab, etanercept, mycophenylate mofetil, sirolimus, tacrolimus, cyclosporine, pentoxifylline, theophylline, thalidomide)
- HIV-1/2 antiretroviral therapies
- Investigational agents
- Cytotoxic chemotherapy
- Systemic or topical glucocorticoids
- Anabolic steroids (physiologic testosterone replacement therapy is not exclusionary)
- Lipid-lowering drugs, including fish oil and omega-3 fatty acids
- Blood pressure-lowering drugs
- Anticoagulants
- Thyroid replacements
- Sildenafil, vardenafil, or tadalafil within 72 hours (before or after) of each main study visit
  - 1. Precautionary Medications
- None

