6.2.2 Main Study Evaluations

There will be three main study visits where blood and urine samples will be obtained, anthropometrics performed, and brachial artery ultrasound measurements will be performed. The Week 4 visit will occur as near to Day 28 after entry as possible, but can occur as late as 42 days after entry. The Week 8 visit will occur as near to Day 56 after entry as possible, but can occur as late as 70 days after entry. Each subject will continue to take study drug/placebo until the final study visit is completed.

- - 1. Study Discontinuation Evaluations

Study subjects who complete the entry (Week 0/Day 0) procedures and have taken at least two weeks of study drug but thereafter notify the study team that they will terminate their involvement prior to the Week 4 visit will have their Week 4 evaluations performed as soon as possible after the time of notice of termination. Subjects who notify the study team that they will terminate their involvement prior to the Week 8 visit and have taken at least 6 weeks of study drug will have their study Week 8 evaluations performed as soon as possible after the time of notice of termination. Subjects who notify the study team that they will terminate their involvement within two weeks after the Week 0 or Week 4 visit evaluations have been completed will have no further evaluations performed.

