1. CRITERIA FOR STUDY DISCONTINUATION

- Request by the subject to withdraw
- Request of the primary care provider if s/he believes the study is no longer in the best interest of the subject
- If the subject is found to be pregnant or begins breastfeeding during the course of this study
- If the subject has develops fever, need for systemic therapy for acute or serious illness, or hypotension after screening that precludes completion of the main study visits within the allowed timeframes
- If the patient develops a need for antiretroviral therapy, as determined by the Principal Investigator or by the subject’s primary HIV caregiver
- Requirement for prohibited concomitant medication(s)
- Study drug-related toxicity (see section 7.0 Adverse Event Management)
- Clinical reasons believed life threatening by the physician
- Subject, as judged by the investigators, to be at risk of failing to comply with the provisions of the study protocol as to cause harm to self or interfere with the validity of the study results
- At the discretion of the funding agency

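### A subject who starts an antihypertensive or lipid-lowering drug for a condition that develops on study is kept in by section 4.2 and put out by sections 5.4.1 and 8 (minor)

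*Combined protocol and SAP*

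**What the plan says.** **Stay.** The closing paragraphs of section 4.2 state: "We are specifically excluding subjects with diabetes, hypertension, and dyslipidemia requiring therapy at screening". They then add: "we will not discontinue study participation if these criteria develop during the course of these trials for two reasons". The first reason is generalizability, since these conditions are common with antiretroviral therapy. The second concerns the study drug: "it is possible that reduction of inflammation by PTX may theoretically prevent insulin resistance, hypertension, and hypertriglyceridemia". The text calls these conditions important endpoints to capture.

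The numbered criteria in section 4.2 show what the conditions mean. Hypertension is "receipt of any antihypertensive medication within 28 days prior to screening or systolic blood pressure > 160mmHg at screening". The only lipid criterion is receipt of a lipid-lowering drug; there is no lipid threshold.

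**Leave.** Section 5.4.1 lists among prohibited medications "Blood pressure-lowering drugs" and "Lipid-lowering drugs, including fish oil and omega-3 fatty acids", with no exception for disease that begins on study. Section 8 lists as a ground for discontinuation: "Requirement for prohibited concomitant medication(s".

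**After leaving.** Section 6.2.3 says that subjects who notify the team that they are stopping before week 8 and "have taken at least 6 weeks of study drug will have their study Week 8 evaluations performed". Those who give notice within two weeks after the week 0 or week 4 visit have nothing further done. Removal by the protocol is not mentioned.

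**Analysis.** Section 9.1 sets intention to treat for all analyses, by assigned group and regardless of adherence or completion. Section 9.2 makes change in FMD from baseline to week 8 the primary endpoint.

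**The concern.** An investigator whose subject is started on an antihypertensive or a lipid-lowering drug during the eight weeks cannot follow both instructions. Two investigators could act differently in good faith.

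The choice affects the data. If the subject stays, week 8 FMD is collected on a new co-medication. If the subject leaves, the primary endpoint may not be collected at all. That sits poorly with the intention-to-treat rule in section 9.1 and with section 4.2's own wish to observe these conditions. Section 9 gives no method for missing data. The replacement rule in section 9.2 can restore numbers, but not the missing value of the subject who was randomized.

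**Working it through.** **1. Which subjects meet both rules**

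| New condition on study | 4.2 closing text | 5.4.1 with section 8 | Conflict? |
|---|---|---|---|
| Hypertension, untreated (systolic > 160 mmHg) | stay | not triggered | no |
| Hypertension, on an antihypertensive | stay | leave | yes |
| Dyslipidemia, on a lipid-lowering drug | stay | leave | yes |
| Diabetes, treated or not | stay | antidiabetic drugs are not listed | no |

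The conflict is confined to the two drug-treated rows. Limiting the stay rule to untreated conditions does not remove it. Section 4.2 speaks of dyslipidemia requiring therapy, and its only lipid criterion is drug receipt, so that reading would leave the rule with no lipid content.

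**2. What happens to week 8 FMD if the subject leaves**

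Section 6.2.3 is worded for subjects who give notice. After at least 6 weeks of drug, they have the week 8 evaluations early. Within two weeks after the week 4 visit, they have none. For a subject removed under section 8 there is no instruction, so week 8 FMD is neither guaranteed nor ruled out. Week 4 is the only scheduled on-treatment blood pressure measurement before week 8 (sections 6.1 and 6.3.8.3), so removal soon after that visit is a plausible route.

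**3. How often**

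The documents give no rate for starting these drugs. The only related data are the two 8-week pilots in section 2.3.3.

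- Enrolled: 11 salsalate + 9 PTX = 20. Completed: 8 + 7 = 15.
- The 5 non-completers: 2 transaminase elevations, 1 lost to follow-up, 1 inhaled steroid, 1 cART. No removal for a blood pressure or lipid drug is reported.
- One-sided 95% upper limit for 0 events in n subjects: 1 − 0.05^(1/n).
  - n = 20: 1 − 0.05^(1/20) = 13.9%; × 26 = 3.6 subjects.
  - n = 15 (completers only): 1 − 0.05^(1/15) = 18.1%; × 26 = 4.7 subjects.

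The second figure is the safer limit. Five subjects were not observed for the full 8 weeks, and a loss to follow-up does not exclude a new drug. Both figures are upper limits, not expected counts. They assume that such a drug start in the pilots would have led to removal and been reported.

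Two features point to the low end. On-study follow-up is about 8 weeks. Lipids come from frozen specimens batch-tested at the end (sections 3.3 and 6.1), so a lipid drug could be prompted only by care outside the study.

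**4. Effect on power**

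Inputs from section 9.2: difference 3.5, baseline SD 2.21, correlation 0.30, two-sided 5% two-sample t-test, 20% dropout.

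- SD of change: 2.21 × √(2 × (1 − 0.30)) = 2.615 (plan: 2.62).
- Power from the noncentral t distribution with SD 2.62: 75.8% at 9 per group and 80.6% at 10 per group, so 10 per group reproduces.
- Dropout: 10 / 0.8 = 12.5, rounded up to 13 per group, as stated.

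| Week 8 values | Power |
|---|---|
| 13 vs 13 | 90.4% |
| 13 vs 12 | 89.2% |
| 13 vs 11 | 87.6% |
| 10 vs 10 | 80.6% |
| 10 vs 9 | 78.2% |

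One or two losses of this kind on their own leave power above 80%. Power falls below 80% only if other dropout has already used the whole allowance.

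**The case against.** **The 4.2 text is residual.** It speaks of two studies, and its first reason concerns antiretroviral therapy, which this trial bars. On this view sections 5.4.1 and 8 are the operative rules, and the PTX pilot did remove two subjects who started prohibited drugs (an inhaled steroid and cART). It is fair to say the paragraph may be carried over. But its second reason names PTX and applies here, and the sentence remains in force until it is deleted.

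**The condition alone does not end participation, while the drug does.** This reading works for untreated hypertension. It fails for the drug-receipt part of the hypertension definition and for dyslipidemia requiring therapy.

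**The missing week 8 visit is not specific to this conflict.** This stands. Section 6.2.3 is silent on every removal by protocol, including toxicity, need for cART and intercurrent illness. The clause denying further evaluations is likewise worded for subjects who give notice, so it cannot prove that a removed subject's value is lost.

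**Stronger readings.** A reader might infer that the primary comparison is biased, that power is at risk, or that intention to treat is broken. The documents do not support these. They give no rate by arm from which a direction of bias could be argued. Section 9.2 already allows 20% dropout with replacement above that. Section 9.1 fixes analysis by assigned group and is not itself contradicted. A reader might also infer that any new hypertension or diabetes triggers the conflict, which the table above rules out.

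**Conclusion.** The inconsistency is real and confined to new-onset hypertension treated with an antihypertensive and new-onset dyslipidemia treated with a lipid-lowering drug. The text does not say which rule governs.

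If removal is chosen, week 8 FMD is unsecured rather than certainly lost. This is one instance of a general gap in section 6.2.3.

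The frequency is unknown and probably low: none reported in the pilots, with an upper limit of about 14% to 18% under the assumptions stated. Those limits also assume that the pilot subjects resemble the trial's subjects. No bias and no loss of power is claimed. The point is minor. Confidence is high in the textual conflict and lower in how often it would matter.

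**What to change.** **Preferred.** In sections 5.4.1 and 8, add an exception: antihypertensive or lipid-lowering therapy started for a condition that develops after entry does not end participation. Record the drug and start date on the existing concomitant-medication CRF (section 6.3.4). Keep the subject, take FMD at the scheduled week 8 visit (Days 56-70), analyse it in the assigned arm, and flag it as measured on the new drug.

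FMD should not be brought forward to precede the new drug. The pilot's median gain was 1.5% at week 4 and 4.4% at week 8 (section 2.3.3), so an early value could understate the effect.

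In section 7.4.1, let the investigator omit NTGMD for such a subject if the hypotension risk is judged too high, with FMD still performed. FMD is complete before nitroglycerin is given (section 3.4), and the other nitroglycerin safeguards already apply to everyone.

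**Alternative.** If the sponsor prefers the ban, delete the 4.2 sentence and state in section 6.2.3 that subjects removed by protocol still have FMD at the scheduled week 8 visit.

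**Cost.** The preferred fix takes about one sentence in each of three sections, with no added visit, test or form. A few FMD values would be measured on a vasoactive co-medication, and section 3.4 lists medications among the factors to control. A few NTGMD values may be missing. A new antihypertensive adds some hypotension risk at nitroglycerin testing, which the NTGMD option addresses. No sample-size input changes.

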4.3 Co-enrollment Guidelines

Co-enrollment into other studies will be permitted provided no drugs prohibited on this study will be given in the other study/ies and that the required blood draws do not exceed safe limits when combined with those for this study.

1. STUDY TREATMENT

5.1 Regimen, Administration, and Duration

At study entry, the study pharmacist at the Indiana University Health Investigational Drug Services (at Indiana University Hospital) must receive a prescription from a member of the study team for pentoxifylline 400mg po tid. As 400mg tablets will be provided, this translates to one tablet orally thrice daily. PTX should be taken with meals. Each subject will take PTX for 8 weeks. If the subject’s final main study visit is delayed past 56 days after study entry, then the subject will continue to take study drug/placebo until the final study visit is completed.

Dosage may be reduced by 400mg decrements in the daily dosage in the event of symptoms likely associated with PTX (e.g. nausea, vomiting, dizziness).

- 1. Product Formulation and Preparation

Extended-release pentoxifylline and matching placebo will be provided by the Indiana University Investigational Drug Services. The PTX ER tablets will be supplied as over-encapsulated capsules and will provided with backfill with standardized qualification procedures per FDA regulations. Placebos will match the study drug for color, taste, texture, size, and smell. All study medications will be stored in bulk at the Research Pharmacy at Indiana University Hospital at room temperature 20-35°C (68-77°F). Both PTX and the placebos will be dispensed in a tight, light-resistant container.

- 1. Study Drug Accountability and Dispensing

The study pharmacist at the Indiana University Health Investigational Drug Services (at Indiana University Hospital) is required to maintain complete records of all study drug. Subjects must bring back to clinic all study drug at each visit to examine pill counts (if necessary) and review dosing.

- 1. Concomitant Medications

5.4.1 Prohibited Medications

- Aspirin or other non-steroidal anti-inflammatory drugs (NSAIDS)
  - Anti-inflammatory agents (including, but not limited to, plaquenil, infliximab, etanercept, mycophenylate mofetil, sirolimus, tacrolimus, cyclosporine, pentoxifylline, theophylline, thalidomide)
- HIV-1/2 antiretroviral therapies
- Investigational agents
- Cytotoxic chemotherapy
- Systemic or topical glucocorticoids
- Anabolic steroids (physiologic testosterone replacement therapy is not exclusionary)
- Lipid-lowering drugs, including fish oil and omega-3 fatty acids
- Blood pressure-lowering drugs
- Anticoagulants
- Thyroid replacements
- Sildenafil, vardenafil, or tadalafil within 72 hours (before or after) of each main study visit
  - 1. Precautionary Medications
- None

1. CLINICAL AND LABORATORY EVALUATIONS

6.1 Schedule of Events

| **Evaluations** | **Screening** | **Study Visits** | | |
| --- | --- | --- | --- | --- |
| **-21 to -7 Day(s)** | **Week 0/**  **Entry** | **Week 4**  **Days 28-42** | **Week 8/Closeout**  **Days 56-70** |
| **Documentation of HIV Status** | X |  |  |  |
| **Medical History** | X |  |  |  |
| **Medication History** | X |  |  |  |
| **Concomitant Medications** |  | X | X | X |
| **Pentoxifylline/Placebo Dosing Modifications** |  | Anytime after entry based on adverse side effects | | |
| **Family History** |  | X |  |  |
| **Smoking History** |  | X |  |  |
| **Brief Physical Examination** | X | X | X | X |
| **Signs & Symptoms** |  | X | X | X |
| **Diagnoses** |  | X | X | X |
| **Adherence Questionnaire** |  |  | X | X |
| **Assessment of effective blinding** |  |  |  | X |
| **Height** |  | X |  |  |
| **Weight** | X | X | X | X |
| **Vital Signs** | X | X | X | X |
| **Waist/Hip Circumferences** |  | X | X | X |
| **Serum Creatinine** | X | X | X | X |
| **Calculated Creatinine Clearance** | X | X | X | X |
| **Liver Function Tests** | X | X | X | X |
| **Urine Pregnancy Test** | X | Whenever pregnancy suspected | | |
| **Urine Analysis** |  | X | X | X |
| **Hematology** | X | X | X | X |
| **CD4/CD8 cell counts and percentages** | X | X | X | X |
| **HIV-1 RNA Level (viral load)** |  | X | X | X |
| **Hepatitis B/C Serologies** |  | X |  |  |
| **PTX Levels** |  | X | X | X |
| **Whole blood for Advanced Flow Cytometry for Immune Activation (CD8+/CD38+/HLA-DR+ cells)** |  | X |  | X |
| **Frozen Serum/Plasma/Urine for Glucose, Insulin, Lipids, Albuminuria, Inflammatory and Endothelial Activation Markers** | X | X | X | X |
| **Frozen Plasma, Serum, & Urine for Future Studies** |  | X | X | X |
| **Brachial Artery Reactivity Testing** |  | X | X | X |

- 1. Definitions for Schedule of Events – Timing of Evaluations

6.2.1 Screening Evaluations

There will be one screening visit to determine eligibility. This must be completed within 21 days of entry (Week 0/Day0 Main Study Visit).

6.2.2 Main Study Evaluations

There will be three main study visits where blood and urine samples will be obtained, anthropometrics performed, and brachial artery ultrasound measurements will be performed. The Week 4 visit will occur as near to Day 28 after entry as possible, but can occur as late as 42 days after entry. The Week 8 visit will occur as near to Day 56 after entry as possible, but can occur as late as 70 days after entry. Each subject will continue to take study drug/placebo until the final study visit is completed.

- - 1. Study Discontinuation Evaluations

Study subjects who complete the entry (Week 0/Day 0) procedures and have taken at least two weeks of study drug but thereafter notify the study team that they will terminate their involvement prior to the Week 4 visit will have their Week 4 evaluations performed as soon as possible after the time of notice of termination. Subjects who notify the study team that they will terminate their involvement prior to the Week 8 visit and have taken at least 6 weeks of study drug will have their study Week 8 evaluations performed as soon as possible after the time of notice of termination. Subjects who notify the study team that they will terminate their involvement within two weeks after the Week 0 or Week 4 visit evaluations have been completed will have no further evaluations performed.

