PTX 400mg three times per day, was given to 9 subjects [128]. Two subjects were removed from study at weeks 2 and 5 due to initiation of prohibited concomitant drugs (inhaled steroid for bronchitis and cART for development of Kaposi Sarcoma, respectively) from their primary caregivers. FMD significantly improved after 4 weeks [median absolute increase 1.5%; p=0.04] and improved further at 8 weeks [median absolute increase from baseline 4.4%; p=0.02]. This degree of improvement in FMD has been associated with reduced risk of future cardiovascular events in the general population[21, 22]. Similar to what was observed with salsalate, 8 weeks of PTX resulted in normalization of FMD. Median NTGMD was 16% at entry and did not change over the course of the trial. It should be noted that the magnitude of improvement in FMD was similar regardless of initial FMD. . Looser stools were noticed by most of the subjects, but in none was this considered to be treatment-limiting. There were no drug-related laboratory toxicities.

We also observed in this pilot study a non-significant decline in triglycerides (p=0.09). No other lipid or metabolic parameter changed with PTX. Viral load did not change. Using an in-house HPLC assay, median plasma PTX concentrations were measured at weeks 4 and 8. The median PTX levels at weeks 4 and 8 were 73 ng/mL (270 nM) and 97 ng/mL (340 nM), respectively. There were no correlations between PTX concentrations and FMD response, which may reflect the small sample size of the study or that there is not a dose-response relationship between plasma PTX levels and FMD. We cannot rule out the possibility that intracellular levels of PTX may correlate with FMD response.

We examined the same peripheral blood markers of various potential inflammatory pathways as in the salsalate trial in order to gain insight into the pathways that may be responsible for the improvement in FMD with PTX. Because of the limited power in this pilot trial, we show in Table 1 those markers that we considered to have changed substantially, defined as either a change > 15% or a p-value < 0.05. Data are presented as median (range) due to small sample size.

Table 1. Markers of pathways that were affected by PTX.

| Biomarker* | Mechanistic Pathway | **HIV-infected Subjects Who Completed the 8 week trial of PTX (N=7)** | | |
| --- | --- | --- | --- | --- |
| Baseline  Median, pg/mL | % Change  (median) | P-value |

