#### 9.3.2 Primary Endpoint Analysis

#### The primary outcome is the change in FMD at week 8 of post treatment from baseline. An analysis of covariance (ANCOVA) model will be used to compare the effect of intervention on this outcome variable. The model will include an indicator variable for intervention, baseline FMD, and other potential covariates, including CD4 cell count, HIV-1 RNA level (viral load), age, sex, race, and BMI. We will include covariates one at a time while keeping the intervention and baseline FMD. All covariates except baseline FMD will be excluded from the model if they have insignificant association with the change in FMD. If the response variable does not follow a normal distribution, an appropriate transformation will be used to approximate a normal distribution. The assumption of the constant variance will also be tested, and a transformation will be used if this assumption is violated.

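### Two early-termination rules in section 6.2.3 conflict after a late Week 4 visit: one requires the Week 8 FMD scan and the other rules it out, with no order of precedence

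*Combined protocol and SAP*

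**What the plan says.** Section 6.2.2 sets the visit timing. "The Week 4 visit will occur as near to Day 28 after entry as possible, but can occur as late as 42 days after entry". For Week 8 the target is Day 56 and the latest permitted day is Day 70. The Schedule of Events (6.1) gives the same windows, Days 28-42 and Days 56-70, and lists brachial artery testing at Weeks 0, 4 and 8.

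The early-termination rules follow directly after; the contents list numbers them 6.2.3. There are three sentences.

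- Sentence 1: for notice given ahead of Week 4 by someone with two or more weeks of drug, the Week 4 set is done promptly.
- Sentence 2: subjects giving notice "prior to the Week 8 visit and have taken at least 6 weeks of study drug will have their study Week 8 evaluations performed", again promptly.
- Sentence 3: subjects giving notice "within two weeks after the Week 0 or Week 4 visit evaluations have been completed will have no further evaluations performed".

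Section 9.3.2 defines the endpoint: "The primary outcome is the change in FMD at week 8 of post treatment from baseline". Section 9.3.3 makes the Week 4 change a secondary endpoint. Section 9.1 applies intention-to-treat whether or not the subject completes the study. Section 9 gives no analysis windows and no rule for termination scans.

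**The concern.** Sentences 2 and 3 use different clocks. Sentence 2 counts weeks of drug taken; sentence 3 counts time since the last visit. If the Week 4 visit takes place on Day 28, the two clocks nearly coincide, because two weeks later is Day 42, or 6 weeks of drug. Each day of delay in the Week 4 visit pushes the no-further-evaluations period one day further into the time when sentence 2 already requires the Week 8 set. Site staff then hold two instructions, and whether a primary-endpoint scan exists depends on which one they follow. In a trial planned on 10 evaluable subjects per arm, that should not be left to chance.

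A second, lesser matter is that Day 42 is both the last day of the Week 4 window and the earliest day for a termination scan done as the Week 8 evaluation. The analysis section does not say how such a scan is used.

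**Working it through.** **The plan's own sample size.** Inputs from 9.2: difference 3.5, baseline SD 2.21, correlation 0.30, two-sided 5% t-test, 20% dropout.

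- SD of change = 2.21 × √(2 × (1 − 0.30)) = 2.61; the plan states 2.62.
- Noncentrality at 10 per arm = 3.5 / (2.62 × √(1/10 + 1/10)) = 2.99 on 18 degrees of freedom. Noncentral-t power is 80.6%, matching the stated figure of at least 80%.
- 10 / (1 − 0.20) = 12.5, rounded up to 13 per arm, as planned.

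**Where sentences 2 and 3 both apply.** Assume dosing from Day 0 without gaps, so that 6 weeks of drug is reached on Day 42, and the Week 8 visit due on Day 56. Let v be the day of the Week 4 visit and d the day of notice.

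- Sentence 2 applies when 42 ≤ d < 56.
- Sentence 3 applies when v ≤ d ≤ v + 14, counting exactly two weeks as within two weeks.
- Both apply when 42 ≤ d ≤ min(v + 14, 55).

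| Week 4 visit (v) | Sentence 3 runs to | Conflicting notice days | Count |
|---|---|---|---|
| Day 28 | Day 42 | Day 42 | 1 |
| Day 35 | Day 49 | Days 42-49 | 8 |
| Day 42 | Day 56 | Days 42-55 | 14 |

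Example: Week 4 visit on Day 42, notice on Day 45. More than 6 weeks of drug have been taken, so sentence 2 requires the Week 8 set. Notice came 3 days after the Week 4 visit, so sentence 3 allows nothing further.

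**Cost of losing the scan.** With 9 against 10 evaluable subjects, noncentrality = 3.5 / (2.62 × √(1/9 + 1/10)) = 2.91 on 17 degrees of freedom, and power is 78.2%. The loss is about 2.4 percentage points. Power falls to 75.8% only if one subject is lost in each arm.

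**Day 42 overlap.** A late scheduled visit on Day 42 is a Week 4 evaluation. A termination scan on Day 42 is a Week 8 evaluation, up to 14 days before the Week 8 window opens. A subject giving notice on Day 42 with the Week 4 visit still pending meets sentences 1 and 2 together. The pilot in 2.3.3 measured FMD only at Weeks 0, 4 and 8, so the effect at Day 42 is not known.

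**The case against.** The intent can largely be recovered. The 2-week and 6-week thresholds mirror the two-week periods after Week 0 and Week 4, and sentence 3 reads naturally as the residual case. The conflict needs a delayed Week 4 visit and then notice within a short interval. In the pentoxifylline pilot the two removals came at weeks 2 and 5, before 6 weeks of drug. Section 9.2 also replaces subjects if dropout exceeds 20%. All of this stands as an argument about frequency and size. It does not settle which sentence governs, and the residual reading is not written down.

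A reader might go further and infer that 6-week scans are filed as Week 8 and bias the primary result by a known amount. The documents do not support that. Section 6.2.3 says which evaluations are performed, not how they are analysed, and the Week 8 label can be read as a list of procedures, since that visit adds flow cytometry and the blinding question to the Week 4 set. It is true that the pilot FMD "improved further at 8 weeks [median absolute increase from baseline 4.4%; p=0.02", against 1.5% at Week 4. But any figure for Day 42 is a line drawn between medians from a pilot with 7 completers.

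Nor does it follow that termination scans should leave the Week 8 comparison. Keeping them fits the intention-to-treat principle in 9.1. As an illustration only, put the Day 42 effect midway between the pilot medians: (1.5 + 4.4) / 2 = 2.95, or 67% of 4.4. One such scan among 10 pentoxifylline subjects lowers the expected difference to 3.5 × (1 − 0.1 × 0.33) = 3.38, with power 78.0%. Dropping that subject gives 78.2%. There is no material gain from exclusion.

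**Conclusion.** The contradiction between sentences 2 and 3 of section 6.2.3 is real. It affects 1 to 14 notice days before Day 56, depending on when in its window the Week 4 visit falls; even an on-time Day 28 visit collides on Day 42. The counts assume dosing from Day 0 without gaps and a Week 8 visit on Day 56. The consequence is the possible loss of a primary-endpoint scan that the plan already calls for. One such loss from 10 evaluable per arm takes power from about 81% to about 78% under the plan's difference and SD. The case should be uncommon and the effect small, and the planned sample size is unaffected.

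On the secondary point, the defect is that section 9 is silent on how a termination scan from Day 42 onward is analysed. The size of any dilution from counting such a scan as Week 8 is unknown.

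**What to change.** 1. In 6.2.3, limit sentence 3 to subjects who have not taken at least 6 weeks of study drug, so that the Week 8 evaluation required by sentence 2 is always done.
2. Record for every termination scan the actual day since entry and the day since last dose.
3. In 9.3.2 and 9.3.3, say how termination scans are analysed. The default would be to keep a scan done as the Week 8 evaluation in the main intention-to-treat comparison, unless the sponsor prespecifies otherwise before unblinding. Add a sensitivity analysis that either excludes scans outside Days 28-42 and 56-70 or uses the actual day.

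The cost is one qualified sentence in 6.2.3, a short addition to section 9.3 and one extra analysis. Disc labels already carry the specimen date (6.3.8.11), and dosing interruptions and discontinuations already go on the CRFs (6.3.5), so little or no new data collection is needed. Subjects in the conflict period would attend for a Week 8 evaluation that sentence 2 already requires.
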